#### Process evaluation

The aim of the process evaluation is to assess the implementation of the intervention, explore the contexts where the intervention was effective (or not) and examine the experiences and acceptability of those delivering and participating in the study.

Quantitative elements of the process evaluation (attendance, number of contacts and completion rates) will be summarised by descriptive statistics. A nested qualitative study will analyse transcribed interviews supplemented with video recordings, observations and field notes. A coding framework will be developed, and data sets analysed thematically with triangulation from different data sources. PPI groups will be consulted about emerging themes.

### Plans to give access to the full protocol, participant-level data and statistical code {31c}

The full protocol will be available upon reasonable request. Participant-level data and statistical code will be accessible through the University of Bristol Research Data Repository.

## Oversight and monitoring

### Composition of the coordinating centre and trial management committee {5d}

This RCT is one workstream within a wider NIHR Programme Grants for Applied Research programme of research: *Reaching Everyone Programme of Research On Violence in diverse Domestic Environments* (REPROVIDE). A management committee, including all co-investigators manages the programme, including this trial. A trial management group (TMG) consists of the chief investigator, principal investigators of each workstream, programme manager, statisticians, health economists and researchers. A programme executive committee (EC) consisting of academics, service providers and trial collaborators also provides guidance and oversight.

Strategic and governance oversight is provided by an independent programme steering committee (PSC).

### Composition of the data monitoring committee, its role and reporting structure {21a}

An independent DMEC reviews study progress and safety data as provided by the TMG, and any ethical issues in keeping with the DMEC charter and reports to the PSC. The PSC has the authority to stop the trial should there be significant safety issues or cause for concern.

As previously mentioned, there are two PPI groups for the research. A group of female victim/survivors who had experienced DVA and a separate group of men who had attended and completed a DAPP (either the REPROVIDE DAPP or another DAPP). Initially, the men’s PPI group also provided an opportunity for men to attend an RPG in a supportive environment order to reflect on the challenges to maintaining positive behaviour change. The men are not paid for their time, but a meeting venue is provided. Halfway through the trial this double function stopped, and the men’s PPI group was reformed in a similar way to the women’s PPI group with all PPI members being invited to take part solely for the purpose of supporting the research and paid as consultants for their time and expertise. Both PPI groups are consulted two–three times per year on the design of the research and the intervention, including questionnaire content and which validated quality of life measure to use, recruitment materials and terminology. Two PPI members are also invited to attend the PSCs and ECs.

### Adverse event reporting and harms {22}

Given the complex nature of this participant population, there is a high risk to the safety of the participant, their (ex)partner(s), any children they have contact with, and to a lesser extent, to the facilitators delivering the intervention and to the researchers. Where possible, female (ex)partners will be notified of their male partner’s potential participation in the study and after (male) recruitment, all female (ex)partners will be contacted again about allocation, to check that they received that communication, offered signposting and invited to take part in the study.

Safeguarding of the (ex)partner and any associated children are of paramount importance; indeed, (ex)partners of participants in the intervention arm will be offered support from the WSW regardless of whether they wish to take part in the study. The WSW will communicate closely with the local DAPP coordinator/facilitators to be aware of any changes in risk while the male participants are undertaking the programme.

All partner organisations will be alert to and report any serious incidents to the research team where they have been made aware of hospitalisation of study participants, or incidents involving serious violence which they feel the research team should be made aware of. This may be through direct disclosure from participants themselves, or through indirect means—for example, regular police reports or local court proceedings. Health-related incidents will follow conventional adverse event (AE) and serious adverse event (SAE) reporting procedures. All SAEs will be assessed for intensity, causality and expectedness by the programme clinician and reported to the sponsor, study oversight committees and Research Ethics for monitoring and review as necessary.

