#### Domestic abuse perpetrator programme

The DAPP intervention is a 23-week group programme with an initial full risk assessment and at least three additional one-to-one sessions. The two-and-a-half-hour weekly sessions are delivered by two DAPP facilitators (ideally, male/female dyads to model good gender role behaviours) from the local provider organisation. The programme runs as a rolling programme allowing new intakes of participants to join every 4 or 5 weeks. Intake weeks depend on the session focus, with certain sessions (such as *Sexual Respect*) being considered too difficult to be an introductory session for a new group member. The sessions are structured to follow the REPROVIDE DAPP manual whose elements include goal identification and goal setting, recognising abuse, denial and minimisation, intents of violence, basic anger management, identifying urges to perpetrate abuse and cooling down strategies, basic cognitive behavioural therapy, effects of DVA on partners and children, participant’s own childhood experiences, impacts on children, active listening, conflict resolution, masculinity, beliefs and expectations, sexual respect, attachment styles, building empathy, loving relationships, emotional abuse and accountability.

Individual sessions led by the DAPP coordinator are tailored to participants’ needs following initial and ongoing assessment with referrals and signposting to other services as needed, such as specialist support for substance abuse. Possible individual interventions may include deconstructing specific incidents of abuse or planning discussions with partners or children. To support quality assurance for the programmes, all our delivery partner organisations were already Respect-accredited or in the processes of accreditation.

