#### Support and information sharing intervention for (ex)partners

The intervention for the female (ex)partners linked to men randomised into the intervention arm is the offer of one-to-one support from a women’s safety worker (WSW) for the duration of the group programme (irrespective of whether the man attends or completes the programme) and for up to 6 months after the programme ends, mirroring the men’s potential participation in the weekly groups and RPG. The WSW assesses risk and provides support and advocacy. The support is offered either face-to-face by telephone or online (see Supplementary Information: RESPONSE TO COVID-19 PANDEMIC). Contact is tailored to need. To manage risk for the (ex)partner and any children, the DAPP facilitators and the WSW regularly share information on an ongoing basis. In some cases, a male participant may have two (ex)partners receiving support. In these cases, where possible, a second WSW would support the second partner.

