#### Usual care control arm

Men allocated to the usual care control arm will not receive any intervention or referrals from the research team. However, they are free to access any other services available to them. The research team may signpost the men to other appropriate services (for example mental health or substance abuse services) if appropriate. All women—regardless of their (ex)partner’s allocation—will be signposted to local and national women’s support services by a member of the research team dedicated to providing contact to the (ex)partners.

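### Serious incidents are reported by organisations whose trial contact after randomisation is with the intervention arm, so control-arm incidents are likely to be under-recorded and by-arm comparisons may be biased

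*Protocol article*

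**What the plan says.** The section on adverse event reporting and harms {22} names who reports: "All partner organisations will be alert to and report any serious incidents to the research team". The duty covers hospitalisations they learn of and "incidents involving serious violence which they feel the research team should be made aware of", so the threshold for violence is a matter of judgement. They may learn of events by direct disclosure or indirectly, "for example, regular police reports or local court proceedings". A separate sentence adds: "Health-related incidents will follow conventional adverse event (AE) and serious adverse event (SAE) reporting procedures".

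Contact between these organisations and participants is described in the intervention sections. For men in the programme, "weekly sessions are delivered by two DAPP facilitators" over 23 weeks, with at least three further one-to-one sessions and an optional monthly relapse prevention group for up to 6 months. Their (ex)partners are offered a women's safety worker during the programme and for up to 6 months afterwards, and "the DAPP facilitators and the WSW regularly share information on an ongoing basis". For the other arm, "Men allocated to the usual care control arm will not receive any intervention or referrals from the research team", and control (ex)partners are signposted to support services. The section on implementation of allocation {16c} says the result is shared straight away with the service provider.

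The DMEC reviews safety data supplied by the trial management group and reports to the PSC. "The PSC has the authority to stop the trial should there be significant safety issues or cause for concern".

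**The concern.** The people asked to notice and pass on serious incidents have regular trial contact with one arm only after randomisation, they know the allocation, and they judge which violent incidents to report. If the same incident is more likely to come to light in the intervention arm, a comparison of recorded incidents by arm partly measures contact and not harm.

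Two errors are possible. Equal true risk could look like an excess with the programme, or a real reduction could be hidden. Alternatively, a real excess could be explained away as closer observation. Both matter because the PSC can stop the trial on safety grounds and because serious violence is the harm most specific to this population.

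**Working it through.** The article states no figure on this point. The check sets the reporting routes side by side and then shows how far unequal detection could move a comparison.

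**Step 1. Routes by arm after randomisation**

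| Route | Intervention arm | Control arm |
|---|---|---|
| Partner-organisation report through contact with the man | Weekly groups, one-to-one sessions, relapse prevention group | No trial-provided contact |
| Partner-organisation report through the (ex)partner | Safety worker offered, even if she declines the study | Signposting only |
| Partner-organisation report through police or courts | Possible | Possible |
| Questionnaires at 4, 8 and 12 months, checked for risk {23} | Yes | Yes |
| Text contact every 6 to 8 weeks {18b} | Yes | Yes |
| Conventional adverse event procedures {22} | Yes | Yes |
| Police-recorded incidents, 12 months after randomisation | Yes | Yes |

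**Step 2. Do the shared routes close the gap?** Not clearly.
- The sample size section allows for 40% attrition, so many questionnaires may not come back.
- The texts are described as a retention measure, not as a way of asking about incidents.
- The conventional procedures are stated for health-related incidents. Serious violence as such falls under the partner-organisation sentence.
- Police records are the strongest common source, but they are listed as a secondary outcome and not as a feed to the DMEC.
- The gap is widest for women who decline the study. In the intervention arm they may still have a safety worker. In the control arm no continuing contact is described.

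**Step 3. Size under assumptions.** Let s_int and s_ctrl be the shares of true incidents that are recorded in each arm. Then:

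apparent rate ratio = true rate ratio × s_int / s_ctrl

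The inputs from the article are 316 men and 2:1 allocation, so 316 × 2/3 ≈ 211 and 316 × 1/3 ≈ 105. The detection shares are assumptions, because the article gives none.

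| s_int | s_ctrl | Apparent rate ratio if true ratio is 1 | Ratio of raw counts, (211 × s_int)/(105 × s_ctrl) | True ratio that would appear as 1 (s_ctrl/s_int) |
|---|---|---|---|---|
| 0.8 | 0.8 | 1.00 | 2.01 | 1.00 |
| 0.8 | 0.6 | 1.33 | 2.68 | 0.75 |
| 0.8 | 0.4 | 2.00 | 4.02 | 0.50 |
| 0.8 | 0.2 | 4.00 | 8.04 | 0.25 |

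As an example, take a true risk of 10% in both arms (also assumed) with detection of 80% and 40%. The expected recorded incidents are 211 × 0.10 × 0.8 = 16.9 and 105 × 0.10 × 0.4 = 4.2. Complete recording would give 21.1 and 10.5. Both arms are under-counted, the control arm by more. The last column shows the opposite danger: at 80% against 40%, a programme that halved serious incidents would appear to have no effect on them.

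**The case against.** The strongest reply is that the article never proposes to compare the arms on partner-organisation reports. It describes a safeguarding duty and case-level review of serious adverse events, and says only that the DMEC sees what the trial management group supplies. Harm to partners is itself the outcome of this trial and is measured in both arms by the ABI-29, the ABI-R and police records. The local DAPP coordinator also meets every man before randomisation, control participants may use other services, and the organisations may hear of control-arm incidents from police or courts. The DMEC charter, the analysis plan and the full protocol are not shown and may deal with all this.

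Much of that stands, and it limits the point. A reader might infer that these organisations see the intervention arm only, that the safety picture given to the committees rests on their reports alone, or that the intervention-arm count is inflated. The documents support none of these. Control contact with a partner organisation is not ruled out, other routes exist, and closer contact does not create incidents.

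What the reply does not remove is the arrangement the article itself sets out: a named reporter with a discretionary threshold, knowledge of allocation and trial contact concentrated in one arm, with no counterpart in the other. The outcome measures do not fully replace incident reports either. Questionnaires are subject to attrition, and police records are not described as reaching the DMEC.

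**Conclusion.** The point holds in a limited form. Ascertainment of serious incidents differs by arm by design. The likely result is under-recording in the control arm, so any by-arm comparison that includes partner-organisation reports may be biased against the intervention or may mask a benefit.

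The size cannot be determined from the article. Across the assumed detection shares, the apparent rate ratio under equal true risk runs from 1.0 (no distortion) to 4.0. Where the trial falls depends on how far the shared routes make up for the difference in contact. The ratio of about 2 in raw counts from 2:1 allocation disappears once rates per man are used. The conclusion assumes that regular contact makes it more likely an incident becomes known, and that by-arm incident data reach the DMEC, the PSC or the final report.

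**What to change.** 1. Record the source of every serious incident: partner organisation, questionnaire, police record, or other.
2. In reports to the DMEC and PSC and in the final report, give incidents as rates per man randomised, by arm and separately by source.
3. Rest the between-arm comparison of harm mainly on sources collected in both arms, that is police records and the 4-, 8- and 12-month questionnaires. Show questionnaire return by arm beside it, because attrition could differ in an unmasked trial.
4. Keep partner-organisation reports fully visible to the DMEC by arm, flagged as subject to unequal ascertainment. They should not be withheld from an arm view, because they may be the most timely signal of real harm.

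Individual case review, reporting and safeguarding duties do not change. The cost is one extra field on the incident form and one more table. The common-source comparison will arrive later than the partner-organisation reports. If the DMEC charter or full protocol already provides for this, a sentence in the harms section pointing to it is enough.

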### Frequency and plans for auditing trial conduct {23}

The DMEC and PSC both meet twice a year and review the conduct of the trial. The DMEC and PSC meetings are linked and in a sequence, so that any concerns raised in the DMEC are passed to the PSC. Examples of issues raised in the DMEC are the routine monitoring and checking of returned questionnaires for risk and safeguarding purposes (July 2022) and a review of serious adverse events and adverse events (March 2023).

### Plans for communicating important protocol amendments to relevant parties (e.g. trial participants, ethical committees) {25}

Any substantial amendments to the trial protocol will require approval of the South Central Oxford B NHS Research Ethics Committee. Minor amendments will be notified to and recorded by the study sponsor, the University of Bristol. Recruitment material and the patient information sheets will be updated if amendments involve changes to eligibility criteria.

### Dissemination plans {31a}

A publication plan will be drafted as part of a wider dissemination and knowledge mobilisation strategy. Findings will be disseminated via final report and peer-reviewed publications, as well as guidance and briefing reports for professionals, commissioners and policymakers.

Participants who have asked to be kept informed will be provided with the findings and we will take advice from our PPI representatives as to how best to provide this in accessible formats.

## Discussion

The fully powered trial will provide robust evidence of the effectiveness and costs of a domestic abuse perpetrator programme. The intervention and study design are built on a broad evidence base, with input and consultation from experts, stakeholders and PPI members and with particular emphasis on the safety and health outcomes of the female victim/survivor partners and ex-partners.

The embedded process evaluation will provide further insights in the mechanisms and barriers, experiences and contexts of participants and their journey through a perpetrator programme. Economic evaluations have been absent in prior studies of perpetrator programmes. Therefore, this study seeks to address this omission and will benefit from the use of broader perspectives.

## Trial status

The current protocol is version 8, 22nd September 2022. Recruitment began on the 21st Oct 2019, but was somewhat delayed as a result of COVID-19. Approximate date when recruitment will be completed for male participants: June 2023, and for female participants, July 2023. Follow-up of participants will continue for another 12 months, until June/July 2024.

## Data Availability

The quantitative datasets generated and analysed during the study will be available to bona fide researchers on reasonable request at the University of Bristol Research Data repository. The qualitative and police datasets generated and analysed during the study will not be publicly available due to the highly sensitive nature of the data which might place victims/survivors of domestic abuse at further risk.

## Abbreviations

BNSSG: Bristol, North Somerset and South Gloucestershire
DAPP: Domestic abuse perpetrator programme
DVA: Domestic violence and abuse
NICE: National Institute for Health and Care Excellence
PPI: Patient and public involvement
RPG: Relapse prevention group
WSW: Women’s safety worker
